### Lokomat intervention protocol

At the start of the child’s Lokomat intervention block, there are two initial fitting/acclimatization sessions, and then 16 twice-weekly Lokomat sessions over an 8- to 10-week period. Fitting the child and acclimatization on the Lokomat is done as outlined in the Lokomat User Manual (Hocoma AG, Switzerland, www.hocoma.com). The goal is to ensure that the child is comfortable in the exoskeleton (e.g., right fit of straps and cuffs, alignment set within a tolerable range of movement) as well as on the treadmill mechanism, and that the child is able to follow the PT’s instructions and to indicate any discomfort. The Lokomat intervention is designed as a standardized protocol, and the content and method for progressing settings on the Lokomat are outlined in Additional file 2. The home program component is limited to basic stretching, strengthening exercises and/or walking practice that the child was on pre-study.

The Lokomat treatment sessions start with 10–20 min on the Lokomat, increasing as tolerated within three sessions to the 30 min maximum target time for this study (Mayr et al. 2007). Four parameters are adapted to the ability, strength, and endurance of the child: body weight support provided; walking duration; ambulation velocity; and guidance force provided to each leg. Guidelines for parameter adjustments are provided in Additional file 2 along with suggested protocols in the Lokomat User Manual, which will inform the setting changes the therapist makes throughout the session. These adjustments will be made to target the child’s gait goals. If a child is unable to keep up with any of the progressions, adjustments will be carried out to a lesser extent or reversed. From a content perspective, the motor-learning based protocol follows both the Lokomat guidelines for encouraging lower limb selective muscle/joint activation and motor learning, and also includes a listed series of upper body tasks that can be done while walking (e.g., throwing a ball, hitting an overhead object) to encourage multi-tasking and improved posture. Use of Lokomat virtual reality games and provision of visual biofeedback are also permitted to promote engagement and feedback. Each session is followed by 5 min of rest before a 5-min overground gait training session to reinforce the Lokomat session gait focus outside of the Lokomat.

Information on the body weight support provided, walking duration, ambulation velocity, and guidance force provided to each leg are recorded in the child’s treatment log as they occur during the session along with details of any breaks or “free rides” (time spent passively) in the Lokomat. In keeping with the principles of motor learning, the goal is to optimize active participation and keep passive walk time to a minimum. The Lokomat computer also continuously tracks all of the settings used throughout the session and provides setting-based information related to any safety stops initiated by the Lokomat. Safety stops occur in reaction to movement forces from the child that are outside of the parameter boundaries of the Lokomat for that child.

### Gait-related PT intervention protocol

This intervention has been created as a motor-learning outpatient program that requires intensive PT guidance, coaching and therapy equipment. At the start of the child’s PT intervention block, there is one acclimatization session to introduce the child to the PT gym equipment and surroundings, and then 16 twice-weekly PT sessions over an 8- to 10-week period. Each PT session consists of 35 min of active treatment with 10 additional minutes of introduction and wrap-up conversation, which parallels the 30 min of Lokomat walking, 5 min of overground walking and similar period of conversation times in the Lokomat group.

The PT session follows a manualized protocol created specifically by Holland Bloorview Child Development Program PTs in conjunction with study co-PIs (see Additional file 3). This GMFCS level-specific PT program is grounded in current evidence-informed clinical practice. From a content perspective, it is menu-based with delineation of key categories of treatment focus. Treatment components are provided within each of these categories. Virtual reality (VR) interventions are permitted as these are now a standard part of PT treatment (Wang and Reid 2011). Treadmill training is allowed to a maximum of 10 min, but body weight support is not permitted as per design in Mayr et al. (2007). This avoids potential contamination through introducing elements of the weight-relieving and limb guidance gait component of the Lokomat protocol into the PT intervention. Other interventions to be avoided are those that are outside mainstream PT (e.g., Cuevos Medek, conductive education techniques) or focus on changes to body structures (e.g., lower limb Botox, inhibitive casting, osteopathy, kinesiotaping).

The PT is at liberty within each session to choose treatment categories and components that link with the child’s goals (as documented at the start of the intervention phase) and progress those goals as they see appropriate based on their clinical judgment. Each component that is given is recorded in the child’s treatment log at the end of the session along with the area of primary focus of the activity (chosen from a list of areas that include balance, strength, agility, gait quality, walking endurance, etc.), details of repetitions, equipment use or settings, and number of minutes spent on each activity. As with the Lokomat arm, the home program is limited to the basic stretching and strengthening exercises and walking practice that the child was on before they entered the study. For children who start in the PT arm, this will help to reduce the possibility of carryover of home treatment ideas from the PT intervention into the Lokomat phase (contamination).

### Study intervention PTs

There are 12 paediatric PTs (all specialists in working with children with CP or brain injury) who were specially trained as described below to provide the Lokomat and PT interventions. Each child is assigned to a study treatment team consisting of two PTs who share responsibility for the twice-weekly treatment sessions. Use of a two-member intervention team is consistent with typical models of service delivery in which a PT and PT Assistant (PTA) share responsibility for a child’s treatment. This team approach also promotes adherence by permitting maximum scheduling flexibility for families from Monday through Sunday, ensuring a spacing of two to three days between the twice-weekly sessions. The same two-PT team is responsible for provision of therapy to the child across both intervention phases, providing a constancy of rapport and interaction style between the PTs and child/parent across interventions. The advantages of this approach are likely to outweigh any intervention preference bias that might influence the actual treatment given. The consistency of treatment focus between PTs is enhanced through strict guidelines as to what treatment approaches may/may not be used, the menu-based and goal-directed intervention design, and the full documentation of all session components. These standardization strategies are very important in the PT intervention given the greater latitude for individual PT treatment variation.

A PTA is present for the Lokomat therapy intervention arm to assist with child set up to optimize the speed of set up, and help with Lokomat setting changes as well as documentation of setting changes throughout the session. The PTA is not present at the PT sessions unless the PT feels that one is required to ensure safety of the child in the walking-related activities. This additional use of the PTA is fully documented in the session log.

### Training of study intervention PTs and PTAs

#### Lokomat intervention

Certification for Lokomat use involves an extensive 2-day training session led by a Hocoma Lokomat licensed trainer. The first day of training familiarizes the PTs with the Lokomat and allowed practice with each other. At the second training day, PTs practice children with CP. Certification follows practice sessions with each other and with several other children with CP who were already receiving Lokomat therapy at a local clinic and hence not eligible for this study. This training approach ensures sufficient familiarity with the treatment progression protocol. Following approximately 3 months of practice, PTs attend a 1-day review session led by the same Hocoma licensed trainer. PTAs also attended the training sessions with the Hocoma trainer to learn the basic components of set-up of the child into the Lokomat orthosis. While they are not operating any of the robotic features of the Lokomat or altering any settings with the children, they do assist with the set-up and monitoring. Thus, it was felt that they needed to have a full understanding of the operation principles of the Lokomat.

#### Gait-related PT Intervention

The treatments involved in the gait-related PT intervention are a standard part of PT practice and the skills do not need to be taught. However, the process for selecting what is done from the study menu (specified within each of the GMFCS Levels) and treatment restrictions were covered in a 3-h orientation session led by the Co-PI (VW). PTAs are rarely involved in this arm, and when they are, it is to provide physical assistance. Thus, extra training is not required.

## Outcome measures

The primary outcome measures selected directly reflect those used in previous Lokomat studies (i.e., GMFM-66, 6MWT, Timed Up and Go and Canadian Occupational Performance Measure [COPM]) (Russell et al. 2000; Russell et al. 2013; Thompson et al. 2008; Williams et al. 2005; Law et al. 1990), and expand into other ICF areas including movement quality (Quality FM, basic gait assessment of spatiotemporal variables via electronic walkway and observational assessment) (Wright et al. 2008, 2014; Sorsdahl et al. 2008), ROM and spasticity (Tardieu) (Scholtes et al. 2006), advanced gross motor skills (*Challenge* Assessment) (Wright et al. 2012; Glazebrook and Wright 2014), functional abilities (i.e., PEDI Caregiver Assistance and ASK-30) (Haley et al. 1992; Young et al. 2000), and participation/QOL (i.e., step activity monitor, CAPE and KIDSCREEN) (King et al. 2007; Ravens-Sieberer et al. 2007; Bjornson et al. 2014). Collectively, these outcome measures provide comprehensive information in areas of activity and participation in alignment with the WHO ICF framework (World Health Organization 2001). Questionnaires are completed by the parent as well as the child if the child is 8 years or older. Each measure is used at each of the four assessment sessions. Personal motivation characteristics of the child (Dimensions of Mastery Questionnaire [DMQ]) (Miller et al. 2014) are assessed at baseline.

The COPM is completed by the child and parent with the assessor at the end of the assessment session, focusing on activity and participation goals. Since the child is not randomized to an intervention group until after the baseline assessment, these are goals that fit a gait-related functional mobility program generally and are not specific to the Lokomat or PT arms. This it is anticipated that these will be higher-level activity and participation related goals that are suitable to either intervention. Goal attainment scaling (GAS) (King et al. 2000) is done during the first two intervention sessions by the study PT with the child/parent. Working from the COPM goals that were created at baseline by the PT assessor, the study PTs re-script these into measurable GAS goals that fit with the intervention (PT or Lokomat) and what they learned about the child from review of their assessment results. This process allows the GAS aspect to be tied in directly to the perceived possibilities of the intervention arm, and fits with the specific outcome scaling process that is required within GAS, i.e., best suited to highly observable goal areas related to body structure and activity. Collectively it is hoped that the combined use of the COPM and GAS will provide a comprehensive evaluation of the extent and nature of goal accomplishments (GAS), as well as perceptions of performance abilities and satisfaction with abilities (COPM).

Within sessions, measures to monitor pain (Wong-Baker FACES^®^ Pain Rating Scale) (Wong and Baker 1988) and physiological effort (PCERT, heart rate) (Yelling et al. 2002) are obtained by the study PT/PTA. At the end of each treatment arm enjoyment is obtained by the RA using a modified version of the PACES (Moore et al. 2009) so that items evaluated make sense in the context of the Lokomat/PT sessions. A table of the measures (Table 1) provides details as to the GMFCS level each measure is linked with the format of administration (observational measure or questionnaire), time required and administration time points. Detailed information on each measure is provided in Additional file 4.

**Table 1 Tab1:** Table of measures

Measure	GMFCS level	Type of measure/respondent^a^	Time to complete				
AT assessment				Baseline 1	Post-1	Baseline 2	Post-2
*Primary*							
GMFM-66	II & III	O/PT with child	30–45 min	x	x	x	x
6MWT	II and III	O/PT with child	10	x	x	x	x
*Secondary*							
GMFM STAND/WALK barefoot (GMFCS II and III) and with shoes/orthoses (GMFCS III)	II & III	O/PT with child	30	x	x	x	x
Timed Up and Go Test	II and III	O/PT with child	5	x	x	x	x
*Challenge *Assessment	II	O/PT with child	30	x	x	x	x
Quality FM	II and III	O–PT via GMFM video	30–60				
ROM/spasticity	II and III	O/PT with child	10	x	x	x	x
Gait evaluation: GAITRite^®^ walkway system; observational gait scale (video rating)	II and III	O/PT with child	15	x	x	x	x
PEDI-functional skills	II and III	Q/parent	15	x	x	x	x
ASK-30	II and III	Q/child or parent proxy	15	x	x	x	x
KIDSCREEN	II and III	Q/child or parent proxy	15	x	x	x	x
CAPE	II and III	Q/child or parent proxy	15	x	x	x	x
GAS and COPM	II and III	Q–child with parent	15	x	x	x	x
*Other*							
DMQ	II and III	Q/child or parent proxy	10	x			
Done at home							
Step-watch^®^ monitor	II and III	Child wears at home	5 days				
Done at sessions				Before session	Mid-point	End of session	Other time
Rating of exertion (PCERT)	II and III	Q/child	2		x	x	
Heart rate	II and III	O/child	1	x	x	x	
L-WALK (Lokomat session distance)	II and III	Lokomat system measure	N/A			x	
Pain scale (FACES)	II and III	Q/child	2	x		x	
PACES	II and III	Q/child	10				16th session
Motor learning strategy rating instrument (MLSRI)		O/rater scores video of intervention session	30				Session week 2 and 7

^a^Type of measure: O = PT observational assessment Q = interviewer introduced/guided questionnaire

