### Blinding

It is not possible to blind the parent or child or study PT to the study interventions. The study’s PT assessors (a separate group from the treating study PTs) are blinded to the child’s treatment arm. The same assessor evaluates the child at each of the baseline and follow-up sessions. The inability to guarantee full success of the blinding is due to overlapping clinical and research treatment/assessment areas, and the possibility that despite asking them not to, children and parents might inadvertently comment on their treatment session experiences to the assessor. Given the strength of objectivity of the outcome measures at single points in time however, concern about the impact of knowledge of group membership is low (Wood et al. 2008). More importantly, to prevent any influence of knowledge of previous results on current assessments, prior assessment data are not available to the assessor at any of the follow-up assessments. Finally, to verify unbiased scoring on the key observational measures (GMFM-66, 6MWT, *Challenge* Assessment, Timed Up and Go), a non-study RA will select a random sample of 20% of the assessment video-recordings to be scored by an independent PT assessor blinded to the assessment’s order in the evaluation sequence.

The study statistician is blinded to group allocation in all analyses. All data are stored in a secure database using Research Electronic Data Capture (REDCap) (Harris 2012), and are entered by the study RA. Data are de-identified using participant study codes. Access codes will be given to the co-PIs for select data sections (i.e., demographics, individualized goals [for purposes of fidelity monitoring], treatment adherence, adverse event tracking), but lack of access to other outcome areas of the database supports PI blinding to the results during the trial. This is important to keep study communications and decisions free from the influence of knowledge of outcomes.

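### The assessor who scores the GMFM-66 and 6MWT also holds the repeated COPM interview with families who know the arm, an avoidable risk to blinding in the second period

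*Protocol article*

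**What the plan says.** The Blinding section says that the PT assessors "are blinded to the child’s treatment arm" and concedes: "It is not possible to blind the parent or child or study PT to the study interventions". The Randomisation section adds that the study RA tells each family the order. On continuity: "The same assessor evaluates the child at each of the baseline and follow-up sessions".

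The Outcome measures section gives the COPM to that assessor: "The COPM is completed by the child and parent with the assessor at the end of the assessment session". The sentence is not limited to baseline, and the same section says "Each measure is used at each of the four assessment sessions". Table 1 ticks a combined GAS and COPM row at Baseline 1, Post-1, Baseline 2 and Post-2. The section argues that COPM goals are not tied to either arm because the child has not been allocated when the baseline assessment takes place.

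GAS is described differently. The treating study PT sets it in the first two intervention sessions, turning the COPM goals into "measurable GAS goals that fit with the intervention (PT or Lokomat"). Table 1 names no interviewer for the combined row.

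The Blinding section accepts that blinding may fail, through overlapping work areas or a family's unplanned remarks. It offers three protections. Families are asked not to comment. Earlier results are withheld: "prior assessment data are not available to the assessor at any of the follow-up assessments". And "a non-study RA will select a random sample of 20% of the assessment video-recordings" for independent scoring of the GMFM-66, 6MWT, Challenge and Timed Up and Go.

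**The concern.** The article treats loss of blinding as an accident of shared space or a stray remark. It does not notice that its own schedule sits the blinded assessor down with an unblinded family, right after 8 to 10 weeks of one intervention, to discuss how well the child now does on mobility goals and how satisfied they are. Asking families not to mention their sessions is hard to square with asking them to talk about progress.

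The design raises the stakes. With two arms and a cross-over, an assessor who learns the first arm also knows the second, and the same assessor then scores Baseline 2 and Post-2. What is at risk is the blinded scoring of both co-primary outcomes over the second period, which supplies half of the planned change scores.

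**Working it through.** The article gives no figure on this point, so the main check is to trace who does what, and in which order.

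**1. Visit by visit**

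| Visit | Family knows the arm? | Could an earlier COPM interview have disclosed it before scoring? |
|---|---|---|
| Baseline 1 | No, not yet randomised | No |
| Post-1 | Yes | No: the only earlier interview preceded randomisation, and the Post-1 interview follows scoring |
| Baseline 2 | Yes | Yes, at Post-1 |
| Post-2 | Yes | Yes, at Post-1 or Baseline 2 |

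Placing the COPM last therefore protects period 1. The Post-2 interview is harmless because all scoring is finished. The two interviews that matter are those at Post-1 and Baseline 2.

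**2. Reach of the neutrality argument.** The argument rests on allocation not having happened. It covers Baseline 1 only. At the other three visits the family has been told the order.

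**3. Upper bound on exposure.** 40 children × 2 periods = 80 planned change scores, of which 40 are in period 2. All 40 are affected only if every family discloses.

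**4. What a bias would do (illustration).** Let *b* be the arm-directed bias in the period-2 change score (Lokomat minus PT) when the arm is known, and *f* the share of children whose assessor knows it. With balanced sequences, period 1 contributes 0 and period 2 contributes *f·b*, so the cross-over estimate shifts by *f·b*/2. The documents give neither *b* nor *f*. For *f* = 1 and assumed values of *b*, a simulation used 32 children, 16 per sequence. It read the article's SD of 6 as the SD of the within-child difference.

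| *b* (GMFM-66 points) | Shift | Type I error, one-sided 0.025 | Type I error, two-sided 0.025 |
|---|---|---|---|
| 0 | 0 | 0.02 | 0.03 |
| 1 | 0.5 | 0.07 | 0.04 |
| 2 | 1.0 | 0.15 | 0.09 |
| 3 | 1.5 | 0.28 | 0.19 |

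The top row is the simulation's check on the nominal 0.025 (0.0245 and 0.0265 before rounding). Both versions are shown because the article does not say whether its 0.025 is one- or two-sided. The shifts compare with a design difference of 3 points. With *f* = 0.5 and *b* = 2 the shift is 0.5 × 2 / 2 = 0.5.

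A bias of equal size at Baseline 2 and Post-2 cancels in the change score. It does not cancel if the arm first comes out in the Baseline 2 interview, because Baseline 2 has then been scored blind and Post-2 will not be.

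**5. The video check.** Taking one recording per assessment, 40 × 4 = 160 recordings, and 20% is 32, of which about 16 fall in period 2. Expected complete pre/post pairs from a simple random draw: 80 × (32/160) × (31/159) = 3.1, about 1.6 of them in period 2.

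**The case against.** Several counter-arguments have force.

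- **Disclosure is not built in.** A reader might infer that the plan compels the leak and that period 2 is in effect unblinded. The documents do not support that. COPM goals are meant to be general, performance and satisfaction can be rated without naming the arm, and families are asked not to comment. The plan schedules a conversation in which disclosure may happen, and no more than that can be said.
- **The limitation is acknowledged.** The Blinding section concedes imperfect blinding and names remarks by families. That stands. What it omits is that one such conversation is assigned to the assessor.
- **GAS.** A reader might infer from Table 1 that the assessor also scores GAS, whose arm-specific goals could give the arm away. The text gives goal setting to the study PT, and the table names no interviewer. The row cannot be literal for GAS anyway, since it ticks Baseline 1, before GAS goals exist. This is a text-table mismatch to reconcile, not evidence of an assessor role.
- **Withheld data.** It is tempting to say that re-rating the COPM breaks the rule on prior data. The rule's purpose is to prevent influence from previous results. A goal list is not a score, and the article does not describe the re-rating procedure.
- **The video sample.** The low pair count might be read as showing that the check fails. It does not. Live-minus-video error can be measured on each recording, and its mean compared by arm and visit without pairs.
- **Other channels.** According to the section on training of assessors, they are also trained on several family questionnaires, so moving the COPM does not remove every contact. That stands and limits what the fix achieves.

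**Conclusion.** The point holds as an avoidable weakness in the blinding procedure. The sections on Blinding and Outcome measures, with Table 1, together put the co-primary assessor into goal interviews with unblinded families at Post-1 and Baseline 2, before that same assessor has finished scoring the child. The neutrality argument does not reach those visits.

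The exposure is at most 40 of 80 planned change scores, all in period 2. How many would be affected, and by how much, cannot be learned from the documents, so the bias table shows a range under assumptions and is not a forecast. The conclusion rests on reading the COPM sentence as applying to every visit, as the four-visit schedule implies. It does not rest on any claim about GAS, on a conflict with the withheld-data rule, or on a failure of the video check.

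**What to change.** 1. After Baseline 1, have the study RA take the COPM re-ratings, or at least someone other than the GMFM-66 and 6MWT assessor. The RA already knows the order and administers the PACES.
2. Keep the COPM and GAS goal sheets from the assessor after Baseline 1. Tell the RA not to discuss allocation while working with the assessor on the gait testing.
3. Reconcile the text on GAS with Table 1: say who scores GAS and at which visits, correct the Baseline 1 tick, and state that the co-primary assessor does not score it.
4. Optional: draw part of the 20% video sample as complete pre/post pairs from period 2. This checks change scores directly but covers fewer different children, so it is a trade-off and not a correction.

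Cost: protocol wording and brief COPM training for the RA, with no new staff. The COPM would be elicited by someone who knows the arm, but its raters, the child and parent, know it already. The other family questionnaires remain a smaller route for disclosure.
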